### Measures

Table 1 provides a list of screening, outcome, mediator and moderator measures. Assessments to monitor treatment progress are performed at baseline (T0), after 2 months (post-CRT or SAT and prior to TAU) (T1), and 6 months after the baseline TAU (T2), and after 12 months (T3) This measurement will encompass the same instruments as used at T2. All patients are extensively re-evaluated using (validated or recommended) indices of treatment effect and costs, quality of life, and cognitive and behavioural flexibility, which will entail self-reports, structured clinical interviews, and paper-and-pen as well as computerized neuropsychological tests. All screening and outcome data are collected in a central database using SPSS/IBM [67].

### Screening measures

The Structured Clinical Interview for DSM-IV-TR Axis I disorders (SCID-I) [64] and the Structured Clinical Interview for DSM-IV-TR Axis II disorders (SCID-II) [68] are used to assess diagnostic status. The SCID-I [64] and SCID-II [68] are semi-structured interviews. Both interviews are organized by the DSM-IV classifications. The inter-rater reliability and validity of SCID-I and SCID-II interviews are fair to excellent depending the diagnosis [69] For the present study we used the full SCID-I and only the section on obsessive-compulsive personality disorder from the SCID-II.

### Outcome measures

The primary outcome measures are: 1) disease-specific psychopathology: Eating Disorder Examination Questionnaire (EDE-Q) [70] for AN severity; Yale-Brown Obsessive Compulsive Scale (Y-BOCS) [65, 66] for OCD severity.

The Eating Disorder Examination Questionnaire (EDE-Q) [70, 71] is the self-report version of the Eating Disorder Examination (EDE) [72], a semi-structured interview to evaluate ED psychopathology. The EDE-Q assesses attitudinal and behavioural aspects of EDs over a 28-day period. It has four subscales assessing concerns about shape, weight and eating, and restraint. The EDE-Q consists of subscale scores and a total scale score. The EDE-Q has excellent internal consistency (Cronbach α 0.78-0.93). The subscales have also excellent test-retest reliability over a 2-week period (Pearson r ranging from 0.81 to 0.94) [73].

The 10-item Yale-Brown Obsessive-Compulsive Severity Scale (Y-BOCS) [74] is a clinician-rated, semi-structured interview-based scale that is broadly used to assess obsessive-compulsive symptom severity. The scale has two parts, each with five questions, with each subscale assessing five aspects of OCD pathology: 1) time consumed, 2) degree of interference, 3) distress, 4) resistance, and 5) perceived control. The first subscale gives an obsession score (maximum: 20), the second a compulsion score (maximum: 20), and together yield a total score (maximum: 40). It has a strong internal consistency (Cronbach α .88-.91), inter-rater reliability (r 0.82–0.98), and test-retest reliability in clinical and nonclinical samples were excellent.

The secondary outcome measures are: 1) disease-specific psychopathology: Obsessive-Compulsive Inventory-Revised (OCI-R) [75], 2) quality of life and daily functioning: EuroQol (EQ-5D) [76], Eating Disorder Quality of life questionnaire (ED-QoL) [77], Obsessive Compulsive Disorder Quality of life questionnaire (OCD-QoL) [78], and Work and Social Adjustment Scale (WSAS) [79], 3) cost-effectiveness (direct and indirect health-related costs as evaluated by means of patients’ self-reported QoL ratings and medical and societal burden: Trimbos/iMTA Questionnaire for Costs associated with Psychiatric illness (TiC-P) [80], 4) general anxiety: Beck Anxiety Inventory (BAI) [81], and 5) Depression: Beck Depression Inventory, second revision (BDI-II) [82].

The Obsessive-Compulsive Inventory-revised (OCI-R) [75] evaluates the frequency, and distress experienced of OCD symptoms using six subscales: washing, obsessing, hoarding, ordering, checking, and neutralizing. The OCI-R has good psychometric properties [75, 83, 84] and is sensitive to the effects of treatment [85]. Internal consistency was adequate (obsessing α = .82, washing α = .86, checking α = .88, neutralizing α = .86, ordering α = .90, hoarding α = .90, total scale α = .81 ) and test-retest reliability was excellent (Spearman’s correlations between .79 and .91) [75].

The EuroQol (EQ-5D) [76] is a standardized self-report instrument gauging five dimensions: mobility, self-care, usual activities, pain/discomfort, and anxiety/depression. Each dimension is rated on three levels (no problems, some problems, and extreme problems). Further, the EQ-5D uses a visual analog scale from 0 to 100, on which the respondent marks his general well-being. The EQ-5D is used in a variety of studies to determine health status in a wide variety of patients.

The Eating disorder Quality-of-Life questionnaire (ED-QoL) [77] generates a disorder-specific self-rated quality-of-life score. It consists of 25 items assessing the influence of eating behaviours/body weight in four subscales: psychological, physical/cognitive, financial, and work/school. A total score is calculated as the average of the items of the four subscales. Higher scores indicate a lower quality of life. The ED-QoL has a good internal consistency (Cronbach α = 0.84–0.95), and test-retest reliability (intraclass correlations were .97 for the psychological subscale, .87 for the physical/cognitive subscale, .90 for the financial subscale, .14 for the work/school subscale, and .93 for the total score) [77].

The Obsessive-Compulsive Disorder Quality of Life (OCD-QoL) is a self-report questionnaire [78] gauging the influence of OCD on the respondent’s quality of life. It was adapted from the ED-QOL and thus also has four subscales: psychological, physical/cognitive, financial and work/school, whose 25 items are scored and interpreted similarly.

The Work and Social Adjustment Scale (WSAS) [79] examines to which extent the disorder has caused the patient functional impairment. A total score of 10 or below is normal, with scores of 10–20 indicating significant functional impairment but less severe clinical symptomatology, and scores of 20 and above suggest moderate to severe impairment or more severe psychopathology. The test-retest correlation for the total WSAS score was 0.73 and the scale has an acceptable to good internal consistency (Cronbach alpha 0.79–0.88).

The Trimbos/iMTA questionnaire for costs associated with psychiatric illness (TIC-P) [80] evaluates the utilization of medical services such as the number of contacts with the general practitioner and other care providers (e.g., medical specialists and paramedics) as well as medication used during the last 3 months. The costs associated with the experimental and control interventions delivered during this study will be calculated as recommended in the Dutch handbook on cost calculations in health care [86]. Reference unit prices of corresponding health-care services will be used and cost-utility calculated by relating the difference in direct medical costs per patient receiving CRT + TAU and SAT + TAU to the difference in terms of quality-adjusted life years (QALY) gained (cost-utility), yielding a QALY estimate.

The Beck Depression Inventory, second revision (BDI-II) [82] is a gold-standard self-report measure to assess the severity of depressive symptoms. The BDI-II comprises 21 categories of statements. Respondents are asked to choose the statement that describes the way they felt in the past 2 weeks. Each item is rated on a 4-point Likert-type scale ranging from 0 to 3, with higher scores indicating higher levels of depression. The maximum total score for all 21 items is 63. Score categories range from 0 to 13 (minimal depression), 14 to 19 (mild depression), 20 to 28 (moderate depression), and 29 to 63 (severe depression). The BDI-II has good psychometric properties [87]. The BDI-II shows good validity compared to the Hamilton Depression Rating Scale (Pearson’s r of 0.71). The inventory has high internal consistency (Cronbach α = .91) [88].

The Beck Anxiety inventory (BAI) [81] gauges symptoms of anxiety (such as trembling hands, dizziness, sweating) by means of 21 questions. Respondents indicate if and to what extent they have experienced any symptoms during the past week on a 4-point Likert scale ranging from 0 (not at all) to 3 (severely). The BAI discriminates well between anxious and non-anxious groups and is useful as screening measure for anxiety in a variety of clinical populations. The BAI has a high validity and high internal consistency (α .92).

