### Study aims

The primary goal of the current ongoing study is to examine the treatment enhancing effect of CRT on treatment as usual (TAU, guideline directed therapy) in AN and OCD. The secondary aim is to investigate the cost-effectiveness and budget impact of CRT. The third aim is to study which patient characteristics determine positive benefits from CRT-based treatment enhancement. More specifically, we study several moderators and mediators of response (Table 1).

**Table 1 Tab1:** Measures to assess screening, outcome, mediator and moderator variables

Function	Measure	Instrument	T0	T1	T2	T3
Screening	Diagnostic status	SCID	X			
Primary outcome	AN severity	EDE-Q	X	X	X	X
	OCD severity	Y-BOCS	X	X	X	X
Secondary outcome	OCD severity	OCI-R	X	X	X	X
	Quality of life	EQ-5D	X	X	X	X
		ED-Qol ^c^	X	X	X	X
		OCD-Qol ^b^	X	X	X	X
	Daily functioning	WSAS	X	X	X	X
	Healthcare utilization and production loss	TIC-P	X	X	X	X
	Depression	BDI-II	X	X	X	X
	General anxiety	BAI	X	X	X	X
Mediators	Cognitive flexibility	Stroop	X	X	X	X
		D-Flex	X	X	X	X
		TMT	X	X	X	X
	Response inhibition	SSRT	X	X	X	X
	Central coherence	GEFT	X	X	X	X
	Intolerance of uncertainty	IUS	X	X	X	X
	Perfectionism	CPQ	X	X	X	X
	Self-efficacy	PEPPI-5	X	X	X	X
	Behaviour inhibition/activation	BISBAS	X	X	X	X
	Therapeutic engagement	SRS ^a^	X			
Moderators	Demographics, e.g. sex, age, education level	Interview	X			
	Diagnostic status	SCID-I	X			
	Obsessive compulsive personality disorder	SCID-II-OCPD	X			
	Autism	AQ	X			
	ADHD	CAARS-S:SV ^b^	X			
	Cognitive flexibility	ID/EDS ^b^	X			
	Planning ability	BADS-Zoo-map	X			

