### Design

Figure 1 provides an overview of the study design. In a randomized controlled multicentre trial, we compare two treatment arms, i.e. CRT and, in the control condition, Specialized Attention Therapy (SAT), both delivered in 10 twice weekly sessions as an adjunct to TAU for AN and OCD. Patients are assessed at baseline (T0), directly following CRT or SAT completion and prior to symptom based TAU (T1), at 6 months after T0; (T2), and at 12 months after T0 (T3). All patients receive both oral and written information and are enrolled after they have provided written informed consent.

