### Procedure and randomization

All participating centres adhere to standardized intake and screening procedures. The therapist performing the screening informs patients meeting the inclusion criteria about the study and ask their permission to have a research assistant contact them by phone or in person to invite them to participate in the trial, after which interested patients are sent or given a brochure describing the study. At least 1 week later baseline assessments are carried out after written informed consent is obtained. After baseline assessments patients not meeting inclusion-criteria are excluded. Patients satisfying all the study criteria are subsequently randomized to one of the two study conditions. An independent research coordinator who is not involved in the therapies or assessments uses SPSS/IBM [67] to create a randomization sequence stratified by treatment centre with a 1:1 allocation using random block sizes of 4. Given the nature of the study design, all patients and therapists are aware of the treatment condition (CRT or SAT). Patients are informed that both treatment arms are being investigated as to their potential to enhance subsequent TAU. The therapists delivering CRT or SAT are instructed not to reveal the treatment condition to the research assistant conducting the assessments; unintended violation of assessor blindness is recorded.

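### A 3-month TIC-P recall at visits 0, 2, 6 and 12 months leaves 4 of 12 follow-up months outside every recall window, and the article gives conflicting definitions of which costs enter the cost-utility ratio

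*Protocol article*

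**What the plan says.** All references are to the protocol article.

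- **Recall period.** Outcome measures describes the TIC-P as recording contacts with the general practitioner and "other care providers (e.g., medical specialists and paramedics) as well as medication used during the last 3 months". No other recall period is given.
- **When it is given.** Table 1 (Study aims) lists the TIC-P under "Healthcare utilization and production loss" and marks it at T0, T1, T2 and T3.
- **Visit times.** Measures places T1 "after 2 months (post-CRT or SAT and prior to TAU) (T1"). Design places the later visits "at 6 months after T0; (T2), and at 12 months after T0 (T3"). Measures words the second of these differently: "6 months after the baseline TAU (T2").
- **Randomisation.** Procedure and randomization puts it after the baseline assessments: "Patients satisfying all the study criteria are subsequently randomized to one of the two study conditions". Time before T0 is therefore pre-randomisation time.
- **Which costs.** The secondary-outcome list in Outcome measures names "cost-effectiveness (direct and indirect health-related costs". The TIC-P paragraph in the same section bases cost-utility on the difference between arms in direct medical costs. Analyses says that every relevant cost and effect is included.

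**The concern.** Cost-effectiveness is the trial's secondary aim. A within-trial cost per patient needs resource use over the whole horizon. A fixed 3-month look-back gives that only if visits are no more than 3 months apart, and the intervals here are 2, 4 and 6 months. The first interval is shorter than the recall, so the T1 form overlaps the pre-randomisation period. The other two are longer, so they leave gaps.

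The position of the gaps matters as well as their length. TAU starts after T1, so the first gap is the opening of TAU. The second can contain the end of weekly OCD treatment. The trial asks whether CRT enhances TAU, so these are months in which TAU use could plausibly differ between arms. An analysis plan can impute unasked months but cannot observe them.

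The definition of the cost numerator is a second, independent problem. Direct medical costs alone and direct plus indirect costs can give different costs per QALY from the same data.

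**Working it through.** The article states no coverage figure to reproduce, so the check is interval arithmetic on its own schedule.

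**Inputs.** Recall 3 months (Outcome measures). Post-baseline visits at 2 months (Measures) and at 6 and 12 months (Design). TIC-P at every visit (Table 1).

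**Formula.** A form at visit *t* covers [*t* − 3, *t*]. Coverage is the union of these windows within months 0-12.

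| Form | Visit (month) | Window | Follow-up months covered |
|---|---|---|---|
| T0 | 0 | −3 to 0 | 0 |
| T1 | 2 | −1 to 2 | 2 |
| T2 | 6 | 3 to 6 | 3 |
| T3 | 12 | 9 to 12 | 3 |

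- Covered: 2 + 3 + 3 = 8 of 12 months.
- Not covered: months 2-3 and 6-9, which is 1 + 3 = 4 months; 4/12 = 33.3%.
- Before randomisation: the T1 window contains 3 − 2 = 1 month (−1 to 0), which is also inside the T0 window.
- An untrimmed sum of T1, T2 and T3 would span 9 months, 8 of them after baseline.

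**Sensitivity.**

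- Horizon of 6 months: only months 2-3 are uncovered, 1/6 = 16.7%.
- T2 at month 8, if the variant wording in Measures means six months after TAU starts: the windows are −1 to 2, 5 to 8 and 9 to 12. The gaps are months 2-5 and 8-9, again 3 + 1 = 4 of 12 (33.3%).

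**Where the gaps fall.** Treatment as usual gives OCD patients 20 to 30 sessions, weekly or twice weekly. Take TAU to start at month 2 and 30.4375 days per month.

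- Weekly: 20 × 7/30.4375 = 4.6 months and 30 × 7/30.4375 = 6.9 months, so TAU ends at about months 6.6 to 8.9, inside the second gap.
- Twice weekly: 10 to 15 weeks, or 2.3 to 3.4 months, so TAU ends at about months 4.3 to 5.4, inside the T2 window.
- AN: no TAU duration is stated.

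**Effect on the comparison.** Write *D* for the true 12-month cost difference between arms. The forms see *D* minus the differences arising in months 2-3 and 6-9. Scaling by 12/8 = 1.5 recovers *D* only if the mean monthly difference in the gaps equals that in the observed months.

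**Cost numerator, side by side.**

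| Place | Costs named |
|---|---|
| Outcome measures, secondary-outcome list | direct and indirect |
| Table 1 | health-care use and production loss |
| Outcome measures, TIC-P paragraph | direct medical only |
| Analyses | all relevant costs |

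The third row cannot stand with the others as the definition of one ratio.

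**The case against.** The strongest reply is that the recall sentence describes the questionnaire in general and is not the trial's visit-by-visit instruction. A condensed article may leave adapted recall, record extraction and interpolation to the full protocol or an economic analysis plan. Grammatically, the 3 months could also attach to medication alone. This has some force. But the article states one recall period and one visit schedule, and these do not fit together. The natural reading covers contacts too.

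Part of the cost has another source, because the experimental and control interventions are costed separately. CRT and SAT fall before T1, however, in months that are covered anyway. Whether that costing includes TAU is not stated. Analyses also describes a state-transition model, which could use cost rates from 3-month windows without continuous observation. The article gives its purpose as assessing future scenarios, so this answers the point only in part.

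A reader might infer more than the document supports:

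- *A third of the costs is unobserved.* The third is of time. No cost distribution is given.
- *A pre-randomisation month is counted.* The T1 window includes it, but no aggregation rule is stated and the analysis could remove it.
- *The gap is 40%.* That puts T1 at 5 weeks (1.15 months), when ten twice-weekly sessions could end: (1.85 + 3)/12 = 40.4%. Measures puts T1 at 2 months.
- *The comparison is biased.* Both arms have the same windows, so bias in the observed cost difference requires use to differ between arms inside the gaps. Twice-weekly OCD treatment would end before month 6.

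**Conclusion.** The point holds as a statement about data collection. On the stated recall and schedule, 4 of 12 months (33% of follow-up time) fall outside every TIC-P window, or 1 of 6 months if the economic horizon is 6 months. The article states no economic horizon; the abstract and sample-size section refer to assessments up to 6 months, while Design adds T3 at 12. One pre-randomisation month lies in both the T0 and T1 windows.

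The result assumes that the 3 months apply to contacts as well as medication and that the form is used unmodified at each visit. The size of any error in cost, or in the difference between arms, cannot be derived from the document. What follows is that 12-month costs would rest on extrapolation across the TAU phase, and that a difference confined to the gaps would be missed.

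The conflict over the cost numerator needs no assumption and must be reconciled. Because cost-effectiveness is a secondary aim, neither problem touches the primary efficacy comparison, but both should be corrected.

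**What to change.** 1. **T1 form.** Ask only about the time since T0, or trim the responses to it. The cost is a changed instruction or an analysis rule.
2. **Trial-centre care.** Take TAU and other contacts at the four centres from their records for the full 12 months. This is a data pull, and it also works for patients already past a visit.
3. **Other care.** Choose one of two routes. Asking about the time since the previous assessment (2, 4 and 6 months) covers 12 of 12 months, at the price of more recall error and, in an ongoing trial, mixed recall periods across patients. Keeping 3 months avoids that but needs a prespecified interpolation for months 2-3 and 6-9, with a sensitivity analysis in which the gaps differ from the observed months.
4. **Cost perspective.** Reconcile the secondary-outcome list, Table 1, the TIC-P paragraph and Analyses to one primary numerator, and report the other as secondary. The choice is the sponsor's; most of the present text points to the broader one. State the economic horizon in the same place. The cost is a text change.
5. **T2 definition.** Align the wording in Measures with that in Design, so that the recall windows are fixed.

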*EDQ* Eating Disorder Examination Questionnaire, *Y-BOCS* Yale-Brown Obsessive Compulsive Scale, *OCI-R* Obsessive-Compulsive Inventory-revised, *EQ-5D* EuroQuol, *ED-Qol* Eating Disorder Quality of life questionnaire, *OCD-Qol* Obsessive-Compulsive Disorder Quality of life questionnaire, *WSAS* Work and Social Adjustment Scale, *TIC-P* Trimbos/iMTA Questionnaire for Cost Associated with Psychiatric Illness, *BDI-II* Beck Depression Inventory, second revision, *BAI Beck* Anxiety Inventory, Stroop Stroop task, *D-FLEX* Detail and Flexibility Questionnaire, *TMT* Trail making test, *SSRT* Stop Signal Reaction Task, *GEFT* Group embedded figures Test, *IUS* Intolerance of uncertainty scale, *CPQ* Clinical perfectionism questionnaire, *PEPPI-5* Perceived Efficacy in Patient-Physician Interactions, *BISBAS* Behavioural Inhibition and Behavioural Activation Scales, *SRS* Session Rating Scale, *SCID-I* Structured Clinical Interview for DSM-IV-TR Axis I disorders, *SCID-II* Structured Clinical Interview for DSM-IV-TR Axis II disorders, section obsessive-compulsive personality disorder, *AQ* Autism-spectrum Quotient, *CAARS-S:SV* Connors’ Adult ADHD Rating Scales, self report, short version, *ID/EDS* Intra dimensional-/extra dimensional shift paradigm, *BADS-Zoo* map Behavioural Assessment of the Dysexecutive Syndrome, Zoo Map

^a^ after each CRT/SAT session

^b^ OCD Only

^c^ AN Only

Our research questions read as follows:To what extend does CRT prior to TAU for AN and CBT for OCD enhance treatment outcome?To what extend is addition of CRT to TAU more cost-effective?What are moderators of treatment-enhancing effect of CRT in AN and OCD?What are mediators of treatment-enhancing effect of CRT in AN and OCD?

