### Cognitive remediation therapy

In this trial, CRT is based on the Dutch translation of the original manual by Kate Tchanturia [119] for both patient groups. Comprising 10 twice weekly 45-min sessions, CRT is delivered by psychologists, clinical nurses, and psychology students (at the MSc level), all having been trained by experienced CRT therapists (UD, BvP, LS, DC) who themselves were trained by [name], expert on CRT for eating and weight disorders. Using a range of cognitive lab-based exercises, CRT aims at improving patients’ set-shifting, cognitive flexibility, global information processing skills, and at reducing perfectionism. Table 2 lists the within-session exercises used in the RCT.

**Table 2 Tab2:** CRT exercises

Central coherence tasks	Maps Summarize a letter Hidden words Word-search task Embedded word task
Set shifting tasks	Card Stack Visual illusions Stroop material Switching attention task Switching Time Zones Alphabet task
Perfectionism tasks	Estimation task
Strategy tasks	How to plant a sunflower Complex figure task

For a more detailed description of the exercises, see Tchanturia et al. [119]. With respect to carrying out the exercises, awareness of dysfunctional thinking styles is enhanced. Patients are encouraged to find out how these thinking styles affect their daily lives, and from session 2 onward, homework assignments are given comprising behavioural exercises that are closely linked to real-life skills and tasks to thus stimulate patients to practice more flexible behaviours in their everyday lives.

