### Specialized Attention Therapy (SAT)

SAT has been designed as the control intervention specifically for this trial. SAT is delivered by the same health professionals delivering CRT. The SAT session structure (10 twice weekly, 45-min sessions and homework assignment) is the same as in CRT. However, during SAT, cognitive flexibility, central coherence, global information processing skills, awareness of thinking styles, and reducing perfectionism are not addressed. Instead, after each task patients are asked their opinion on whether they (dis)liked the task. As a treatment rationale, patients are explained that SAT aims at helping them to focus on positive experiences by means of tasks and exercises, where each session–again in line with CRT–comprises different exercises. For an overview of the exercises practiced in SAT, see Table 3; for a more detailed description of the exercises, the SAT treatment manual is available upon request [120].

**Table 3 Tab3:** SAT exercises

Motor tasks	Djenga Mikado Leaning Tower of Pisa Operation Game
Luck tasks	Game of the Goose Ludo Snakes and ladders
Collaboration task	Drawing a picture together
Picture tasks	Spot the differences Viewing a picture
Verbal tasks	Last letter-first letter Incomplete sentences task Poems
Additional tasks	Listening to music Analogies Categories

From session 2 onward, patients are encouraged to engage in similar activities at home that they enjoy.

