### Treatment fidelity

To ensure treatment fidelity for CRT and SAT, the best practices and recommendations from the NIH Behaviour Change Consortium [125] are followed. The number, duration, and frequency of sessions, as well as patient-therapist contact times are kept the same for CRT and SAT. All patient-therapist contacts are formally scheduled to ensure fixed durations. All treatment sessions are audio- or videotaped and an external checker not involved in the trial rates treatment fidelity in a random selection of 10% of the recorded sessions. To evaluate, guide, and approve interventions, and to constrain ‘therapist drift’, all therapists are supervised by expert professionals, and have at least monthly intervision-sessions. After every session, the therapist completes a brief questionnaire to record treatment stage and components delivered. Deviations from the protocol are reported to the supervisor.

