### Analyses

Baseline differences between the CRT and SAT (control) groups and between the participating centres are investigated using χ^2^ tests for categorical variables and ANOVAs for continuous variables. Additional exploratory analyses are conducted separately for AN and OCD.

The data for the primary AN and OCD outcome indices are analysed using linear mixed models (LMM) with the baseline value as a covariate. The mixed models analysing the general efficacy of CRT include a random term for the intercept and fixed terms for condition, time contrasts (T0–T1, T0–T2, T0–T3, T1–T2, T1–T3), and the interactions between condition and time contrasts.

In order to investigate moderators of short- and long-term treatment response, time contrasts are created (T0–T1, T0–T2, T0–T3, T1–T2, T1–T3) by means of dummy coding. Potential continuous moderator variables are standardized. Interactions between condition and the potential moderators are entered into the equation. All analyses on therapy effect modificators are of an exploratory nature. The moderator and mediator analyses are calculated with 5000 bootstraps [126].

To assess the cost-effectiveness of CRT + TAU versus SAT + TAU for ED and OCD, all relevant costs and effects are taken into account. Disease progression is described in terms of transitions between ‘states’, where a patient’s ‘state’ can shift in either direction or remain constant. Estimations of state-transition rates are based on the data from the ongoing trial and the literature, which modelling approach serves to help us assess future scenarios. Costs and effects are calculated in accordance with recommendations in the Dutch guideline for economic evaluation of health care. As a primary assessment we apply a costs-utility analysis that yields a cost per quality-adjusted life years (QALY) outcome, a common cost-effectiveness measure that allows comparison with economic evaluations of other diseases and interventions. The uncertainty estimations are computed using bootstrapping and the results expressed in an acceptability curve. If no intervention is effective, a cost-minimization calculation is performed.

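### The planned cost difference is taken against a trial-only control matched to CRT in contact time, so CRT's own delivery cost largely drops out and research question 2, on adding CRT to TAU, is not answered

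*Protocol article*

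**What the plan says.** Under Study aims, the protocol article states: "The secondary aim is to investigate the cost-effectiveness and budget impact of CRT". Research question 2, in the same section, reads: "To what extend is addition of CRT to TAU more cost-effective". Both concern CRT as something added to usual care.

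The calculation is fixed in two other places. The TIC-P paragraph under Outcome measures says "The costs associated with the experimental and control interventions delivered during this study will be calculated", and then has "cost-utility calculated by relating the difference in direct medical costs per patient receiving CRT + TAU and SAT + TAU" to the QALY difference. The Analyses section sets out its economic methods with the words "To assess the cost-effectiveness of CRT + TAU versus SAT + TAU for ED and OCD".

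On the comparator, the SAT section says "SAT has been designed as the control intervention specifically for this trial". It adds that SAT has the session structure of CRT and is given by the same professionals. CRT itself is described as "Comprising 10 twice weekly 45-min sessions". Treatment fidelity adds: "The number, duration, and frequency of sessions, as well as patient-therapist contact times are kept the same for CRT and SAT".

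The Analyses section also provides for a cost-minimization calculation if no intervention proves effective. No section describes a costing against TAU without SAT, or removes the cost of SAT from the control arm.

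**The concern.** Matching SAT to CRT in therapist time is sound for judging whether CRT's specific content works. It causes trouble when the same contrast is used to decide whether CRT is worth adding to usual care. A clinic that adopts CRT goes from TAU to CRT plus TAU and pays for ten extra sessions per patient. The planned difference charges the control arm for ten sessions of an intervention that exists only in the trial, so the main cost of adopting CRT is subtracted out.

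At stake is a declared secondary aim. A cost per QALY from the planned contrast, reported as the answer to research question 2, would describe CRT with almost none of its delivery cost. The clinical outcome comparison, the randomisation and the sample size are not affected.

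**Working it through.** **Figures in the plan.** The plan states no unit price, expected QALY gain or cost-effectiveness ratio, so there is no economic figure to reproduce. The usable inputs are session counts and lengths.

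**Inputs**
- CRT: 10 sessions of 45 min (Cognitive remediation therapy).
- SAT: 10 sessions of 45 min, same professionals (Specialized Attention Therapy).
- Contact time held equal between arms (Treatment fidelity).
- Reference unit prices applied, and both interventions costed (Outcome measures, TIC-P).

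**Step 1: scheduled contact time per patient**
- CRT: 10 x 45 = 450 min = 7.5 h.
- SAT: 10 x 45 = 450 min = 7.5 h.
- CRT + TAU minus SAT + TAU: 450 - 450 = 0 min.
- CRT + TAU minus TAU without SAT: 450 - 0 = 450 min.

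With the same staff at the same unit prices, the scheduled delivery cost in the planned difference is about zero. For the question asked, it is the price of 7.5 hours.

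**Step 2: what this does to the ratio.** Write C and S for the delivery costs of CRT and SAT. Write K for all other care costs and Q for QALYs, with subscripts crt, sat and tau.
- Planned ratio: (C - S + K_crt - K_sat) / (Q_crt - Q_sat). With C ≈ S, the numerator reduces to K_crt - K_sat.
- Ratio for research question 2: (C + K_crt - K_tau) / (Q_crt - Q_tau).
- The delivery cost missing from the planned numerator is S ≈ C.
- The denominators differ too: Q_crt - Q_tau = (Q_crt - Q_sat) + (Q_sat - Q_tau). The last term is positive if SAT has some non-specific benefit. It is negative if the wait for psychological treatment costs QALYs. The documents do not settle its sign.

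**Step 3: illustration in money (assumed inputs only)**
- At 50 to 150 euro per contact hour: 7.5 x 50 = 375 and 7.5 x 150 = 1,125 euro per patient. With a QALY gain of 0.02 to 0.05, the missing part of the ratio runs from 375 / 0.05 = 7,500 to 1,125 / 0.02 = 56,250 euro per QALY.
- At 50 to 150 euro per session: 500 to 1,500 euro per patient. With a gain of 0.02 to 0.10, it runs from 500 / 0.10 = 5,000 to 1,500 / 0.02 = 75,000 euro per QALY.

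Both illustrations hold the QALY gain and the other care costs the same against either comparator. The width of the ranges shows that only the 7.5 hours comes from the documents.

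**Step 4: the cost-minimization fallback.** If neither intervention is effective, comparing the two arms again gives 450 - 450 = 0 min of scheduled delivery. It would not show that giving neither saves 450 min per patient.

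**The case against.** The strongest defence is that the planned ratio is coherent: costs and effects come from the same two randomised arms. Setting SAT's cost to zero pairs a delivery cost measured against TAU with effects and other care costs measured against SAT + TAU, a comparator that no patient received. The Interventions section defers other psychological treatment in both arms until CRT or SAT is complete, and Measures puts that assessment at 2 months. TAU alone would not carry the delay. This stands, and it is why the randomised comparison should stay and the added analysis must list its assumptions. It does not make the planned ratio an answer to research question 2.

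Three stronger readings are tempting but not supported:
- **The whole ratio is biased towards CRT.** Only the delivery-cost side is clear. A benefit of SAT would pull the other way, and the Discussion says that SAT's validity as a control has not been tested.
- **The budget impact will treat CRT as free.** The article names budget impact as an aim but does not say how it is computed, and CRT's own cost will be available because both interventions are costed.
- **The incremental intervention cost is exactly zero.** The match is of scheduled contact time. The costs are of interventions as delivered, so attendance and dropout could differ by arm. Training or materials might differ too, though the article does not say so.

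One could also reply that the state-transition model, which draws on the literature as well as trial data, repairs the gap. The Analyses section frames that work on the same two arms, so as written it does not. Nor is this a detail left to a fuller document: the article fixes the comparator explicitly in two sections.

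**Conclusion.** The point holds. The economic question is about adding CRT to TAU, while the stated cost difference is against SAT + TAU. CRT's scheduled delivery cost, 7.5 contact hours per patient, essentially cancels, so the plan as written cannot answer research question 2. The delivery-cost side favours CRT as an addition to TAU. The net direction of the cost per QALY against TAU alone is not established, and the euro ranges above are illustrations.

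The conclusion rests on equal staffing, equal scheduled sessions and common unit prices, the first two stated in the article and the third following from its use of reference prices. The cost-minimization fallback shares the defect. The matter is confined to the secondary economic aim.

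**What to change.** 1. Keep the randomised CRT + TAU versus SAT + TAU cost-utility analysis, and label it as CRT versus an attention control.
2. Pre-specify beside it a cost-utility analysis with the SAT delivery cost set to zero in the control arm and the full CRT delivery cost retained. Do the same for the cost-minimization calculation if it is triggered.
3. Base the answer to research question 2 on that second analysis. State its assumptions: SAT has no effect on QALYs or on other care costs, and the delay to TAU has no effect.
4. State that any budget-impact estimate must count the full CRT delivery cost.

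The cost is one extra costing analysis, with no new data collection, since both interventions are already to be costed. The drawbacks are a less favourable cost per QALY for CRT and a comparator that is partly modelled rather than randomised.
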